### Study population

The study population consists of men aged 18 to 44 years at date of diagnosis, born in metropolitan France, with a valid health insurance affiliation. Cases are men diagnosed with seminoma or non-seminoma TGCT (ascertained through histological report), and seen in one of the participating CECOS for sperm cryopreservation. Controls of group A are sperm donors or partners of infertile women having a normal sperm count (>39 million per ejaculate [37]). Controls of group B are partners of pregnant women hospitalized for a pathological pregnancy in the level III maternity (regional maternity) adjacent to the CECOS. Participants have to sign an informed consent form. Subjects unable to write and understand French language, as well as subjects presenting severe psychological or mental disorders, and subjects under legal guardianship are excluded. Controls with a history of cryptorchidism or of TGCT are also excluded. Two controls (one of each group) are matched to each case on age (±2 years) and the recruiting center.

Considering the incidence of TGCT and the CECOS activity, we estimate a 18-month duration to recruit all cases and controls. The recruitment is performed by physicians and/or midwives (investigators). A written permission is asked to cases and controls to contact their mothers (or the closest relative alive, if the mother is deceased or cannot be interviewed). Participants who sign the informed consent receive a document to prepare information prior to the phone interview, including: lifetime residential history, addresses of schools during childhood, parental occupation at subjects’ conception, birth information, and job history. Investigators propose to each case and control to participate in a blood sample collection. Information on subjects is recorded using a protected on-line study platform that generates a unique identification number for each participant. Cases and controls receive a financial compensation for their participation: 20 euros for completion of the interview and 40 euros for participation in both blood sampling and completion of the interview.

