### Environmental exposure assessment

Cases and controls residential history are gathered from 1 year prior to birth to date of the inclusion in the study. Semi-automatized fields in the study platform help to reduce misspellings when entering the questionnaire data. In case of inconsistency between subjects’ and mothers’ information, data provided by the mothers are used. Addresses are geocoded using the database “*BD adresse*” from the French National Geographic Institute (IGN), which contains coordinates of all addresses in France (unit: RGF Lambert 93). Since the coordinates of the database are centered on the postal address, a GIS technician moves manually the point to the center of the household. Using dedicated software (BD Adresse® for ArcGIS Locator), we identify all addresses geocoded with poor precision (at the street level or less) for manual verification or repositioning (when possible). Specific additional questions are added to the questionnaire to help the GIS technician when no street number is available (closest crossing road or point of interest).

The use of infra-red images, based on the greenness reflectance, has been used successfully in previous US studies to reconstruct land use data [39, 40]. Satellites images are available from the Landsat® program from 1972 with an 80 m spatial resolution and from the SPOT® program from 1986 with a 20 m spatial resolution. Based on remote sensing of satellite images and/or photo interpretation of IGN aerial photography (available from 1920’s), we determine the land use around each residence of interest. When data are not available or of poor quality, we assign land use data of the nearest available time period to the residence. Public data from agricultural statistics (Recensement Statistique Agricole, DRAAF) as well as expert assessment are used to validate our land use layer, when needed. The agricultural statistics provide the proportion of each type of crops in each municipality for 1970, 1979, 1988, 2000, and 2010.

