### Statistical analyses

Standard descriptive statistics will be used to describe characteristics and pesticide exposure of cases, controls and mothers/relatives. Exposure variables will be explored using supervised principal component analyses [48]. Risk analyses will be based on conditional logistic regression models, to compute odds ratios for TGCT at different levels of exposure. Exposure variables will be investigated as continuous variables (with appropriate transformation to achieve normality) as well as categorical variables (quartiles or predefined categories depending on variable type). In addition we will create a combined pesticide exposure variable based on pesticide exposure (occupational, environmental and domestic) during prenatal and early postnatal period (PEPPP) and during adolescence (PEA). We will examine PEPPP exposure, PEA exposure, and combined PEPPP and PEA exposure in relation to TGCT risk. The effects of additional potential confounders (other than our matching criteria) on the associations between pesticide exposure and risk of TGCT will be examined and added to the model one by one. Comparison between models with and without adjustment will be used to examine the potential confounding effect of these factors and only factors with relevant changes in the odds ratios will be kept in the final model. Potential confounders include the geographical origin, socio-economic status, tobacco and cannabis consumption, length and weight at birth, birth order, and the familial history of TGCT.

The two control groups will be used first as separate control groups to identify potential major differences. In order to examine whether any of the associations between pesticide exposures and TGCT risk differ by subgroups of known risk factors or by genetic polymorphisms, we will perform additional stratified analyses. Tests for statistical interaction will be used to examine whether any apparent heterogeneity of effect is statistically significant. This will be done by comparing models with and without interaction terms between the risk factor or genetic polymorphisms and the environmental variable (pesticide exposure) with a maximum likelihood ratio test. Sensitivity analyses are planned to explore the impact of potential bias or methodology limitations (such as quality of satellite images, through removing subject born before 1986 having less precise satellite images at time of birth).

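### The image-quality sensitivity analysis cuts at birth in 1986 although the prenatal window opens a year earlier, and it cannot separate image quality from age and birth cohort

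*Protocol article*

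**What the plan says.** All references are to the protocol article.

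- **Statistical analyses.** Sensitivity analyses will explore possible bias and limits of method. The one example given concerns satellite image quality, tested "through removing subject born before 1986 having less precise satellite images at time of birth". The main model is conditional logistic regression.
- **Environmental exposure assessment, images.** Satellite images come "from the Landsat® program from 1972 with an 80 m spatial resolution" and "from the SPOT® program from 1986 with a 20 m spatial resolution". Land use may also come from "photo interpretation of IGN aerial photography", with or instead of satellite images. Gaps are filled by this rule: "When data are not available or of poor quality, we assign land use data of the nearest available time period to the residence".
- **Environmental exposure assessment, time window.** "Cases and controls residential history are gathered from 1 year prior to birth to date of the inclusion in the study". The exposure index is scored for each address and year, and the prenatal period is one of the periods singled out.
- **Objectives.** Prenatal and early childhood exposure is the main target.
- **Study population.** "The study population consists of men aged 18 to 44 years at date of diagnosis". Recruitment is expected to take 18 months. Each case has two controls from the same center, within two years of age.

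**The concern.** The restriction is meant to show whether coarse images affect the environmental result. Two features of the rule work against that.

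First, the cut is placed at birth, while the exposure of most interest is accrued before birth. Some men kept as having good images still depend on pre-1986 imagery for the prenatal window.

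Second, recruitment is short, so dropping early birth years drops the older men. Those kept and those dropped then differ in age at diagnosis, birth cohort and the pesticides in use, as well as in image resolution. The article itself treats pesticide use as period-specific: the crop-to-pesticide matrices depend on crop and period. If the odds ratio changed, a reader could credit or blame the images. If it did not change, a reader could conclude that image quality does not matter. The comparison supports neither conclusion.

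**Working it through.** **Step 1. Which births have 20 m images for the whole prenatal window?**
Let B be the date of birth and S the start of 20 m images. The article gives only the year, so take S = 1986.0, the reading most favorable to the plan. The residential window before birth runs from B − 1 to B. Full coverage needs B − 1 ≥ 1986.0, so B ≥ 1987.0. For a man born during 1986, the share of that window before S is 1987 − B:

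- born 1 January 1986: 1.0, so the whole window predates 20 m images;
- born mid-1986: 0.5;
- born end of 1986: about 0.

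Counting gestation only, the men affected are those conceived in 1985, roughly the births of the first nine months of 1986.

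**Step 2. How many retained cases does this affect?**
From the article: ages 18–44 (18 to under 45, a span of 27 years), 18 months of recruitment, 500 cases. Assumed, because the article does not state them: recruitment starting in 2013 to 2016; ages uniform, or truncated normal with mean 30 or 33 and SD 7; age at recruitment equal to age at diagnosis.

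With uniform ages and recruitment midpoint M = start + 0.75:

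- share of cases kept = (M − 1986 − 18)/27
- share of kept cases born in 1986 = (1/27)/(share kept) = 1/(M − 2004)

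Start 2013: M = 2013.75, kept = 9.75/27 = 36%, born in 1986 = 1/9.75 = 10%.
Start 2016: M = 2016.75, kept = 12.75/27 = 47%, born in 1986 = 1/12.75 = 8%.

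Simulation of 400,000 matched sets per scenario agrees and extends this to the other age distributions. For each distribution, starts in 2014 and 2015 fall between the rows shown.

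| Start | Ages | Cases kept, born 1986 or later | Born in 1986, of those kept | Conceived in 1985, of those kept | Cases kept, born 1987 or later | Median age kept / dropped |
|---|---|---|---|---|---|---|
| 2013 | uniform | 36.0% | 10.2% | 7.4% | 32.5% | 22.9 / 36.4 |
| 2013 | mean 30 | 35.2% | 16.0% | 11.7% | 29.6% | 24.3 / 33.3 |
| 2013 | mean 33 | 22.5% | 19.4% | 14.4% | 18.2% | 24.8 / 34.6 |
| 2016 | uniform | 47.1% | 7.9% | 5.7% | 43.5% | 24.4 / 37.9 |
| 2016 | mean 30 | 53.0% | 11.3% | 8.2% | 46.9% | 26.2 / 35.0 |
| 2016 | mean 33 | 38.0% | 14.6% | 10.8% | 32.4% | 27.0 / 36.0 |

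Of 500 cases, the 1986 cut keeps about 113 (0.225 × 500) to 265 (0.530 × 500). A 1987 cut keeps about 91 (0.182 × 500) to 235 (0.469 × 500).

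**Step 3. How closely does birth year follow age?**
Age at recruitment is the recruitment date minus B, and the recruitment date varies by only 1.5 years. With a 2013 start, every man younger than 2013 − 1986 = 27.0 is kept and every man older than 2014.5 − 1986 = 28.5 is dropped. Only the 1.5-year band between them contains both. With a 2016 start the band is 30.0 to 31.5. The oldest retained man is therefore about 28.5 to 31.5 years, and almost no age range contains both kept and dropped men.

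**Step 4. Matched sets.**
Only sets within two years of the cut can be split. In the simulation about 6–10% of all sets straddle it, and about 1.3–3% of retained cases lose both controls.

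**The case against.** The strongest defense has three parts.

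- **The date suits its stated criterion.** The article judges images at birth, and 1986 is right for that. At most one birth year is at issue. Aerial photographs and the closest-period rule may supply better land-use data for 1985. The combined prenatal and early postnatal exposure also includes time after birth, for which men born in 1986 do have 20 m images. All of this stands and keeps the cut-off problem small. It does not make birth the right reference point for prenatal exposure.
- **Restriction to better-measured subjects is a standard check.** The article says only that it will explore the impact, gives this as one example, and sets no decision rule. This stands: the analysis is legitimate as a check on persistence. It is not a test of image quality.
- **The remedies are imperfect.** A later cut removes more men, and an interaction with an image era defined by birth year is confounded in the same way. This also stands, so the interaction should use the actual image source and carry a stated caution.

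A reader might infer more than the article supports:

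- **That split sets bias the result.** Removal depends on birth date, not exposure, and a set that keeps its case and one control still contributes. The cost is information. Handling of incomplete sets may also be in a fuller plan that is not shown.
- **That this is the only check on the exposure measure.** The land-use layer is validated with agricultural statistics and expert assessment, poorly geocoded addresses are verified by hand, the method rests on an indoor-dust study of 239 homes, and mothers' and sons' prenatal addresses are compared.
- **That a loss of power can be quantified.** The 10% and 15% prevalences under Determination of the sample size are occupational, and the article expects occupational exposure to be less frequent than environmental exposure. It gives no environmental prevalence, and a sensitivity analysis need not have the main analysis's power.
- **That histology differs between kept and dropped men.** Nothing in the article shows this.

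**Conclusion.** The point holds in a limited form. For prenatal exposure the cut is up to one birth year too early: men born in 1986, about 8–19% of retained cases (about 6–14% counting only those conceived in 1985), may still depend on pre-1986 imagery. The larger limitation is selection. Roughly a quarter to a half of cases remain, all aged at most about 28.5 to 31.5, so the analysis can show whether an association persists in the youngest men but cannot isolate image quality from cohort, pesticide period or age at diagnosis.

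The percentages and upper ages rest on the assumed recruitment starts and, for the percentages, on the assumed age distributions. The one-year mismatch and the near-identity of birth year and age follow from the article's own dates, age range and recruitment period. The objection is to a rule the article states, not to detail it leaves out.

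**What to change.** 1. For prenatal exposure, restrict to men whose whole prenatal window has 20 m images (born 1987 or later). Better, define the restriction by the image source actually used for the prenatal address-years, since aerial photographs and the closest-period rule mean that birth year is only a proxy.
2. Apply the restriction by matched set, using the case's status.
3. Also keep all subjects and report an exposure by image-source interaction as a ratio of odds ratios with its confidence interval. Add an exposure by birth-cohort term where image source and cohort can be separated.
4. State that any difference may reflect birth cohort, pesticide period or age, and describe the restricted analysis as a check on persistence.

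Rescoring a sample of post-1986 addresses at both 80 m and 20 m would isolate resolution within the same men. It is optional extra work.

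Cost: slightly fewer men in the restricted analysis and a little more analysis work. With a 1987 cut, the 8–19% of retained cases born in 1986 leave, about 19 (500/27, uniform ages) to 30 (0.530 × 0.113 × 500) of the 500 cases. No new participants or data collection are needed.

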### Steering committee

A Steering Committee has been implemented to oversee the study progress. It is composed of the two principal investigators, a project manager, a doctoral student, study partners, two oncologists specialized in TGCT and eight CECOS representatives. The Steering Committee will meet every 4 months. It will be regularly informed about study progress and of any emerging problems. It will monitor compliance with the study protocol, the quality of collected data and will review scientific reports and publications.

## Discussion

Considering the rarity and latency of TGCT, the case–control design appears to be the most appropriate method for our research. Based on a two-year pilot study, the TESTIS project was optimized to address short comings identified by previous research despite the rarity of the TGCT. In France, around 2000 men are diagnosed with TGCT each year and at least 1100 TGCT patients are seen annually for sperm cryopreservation in the CECOS network. The CECOS have a regional recruitment, and only the CECOS are allowed to cryopreserve sperm in France. Based on our pilot study, loss due to inclusion/exclusion criteria and to non-participation should not exceed 50%. Thus, we estimate that 18 months is long enough to ensure the recruitment of 500 TGCT cases in the 21 participating CECOS.

Testicular cancer and reproduction are sensitive topics. Recruiting the controls through hospital settings aims to facilitate the recruitment of our young male population, as well as managing biological sampling. To ensure that both cases and controls are recruited at a regional level, we decided to select Group B controls among partners of women having a pathological pregnancy. The latter are managed centrally in the regional maternities adjacent to the participating CECOS, while selecting controls among partners of all pregnant women in these maternities would lead to over-representation of the urban population. With a participation of 21 out of 23 CECOS, we assume that our sample is representative to the French metropolitan territory.

In general, young men are difficult to approach and less likely to participate to research than other population groups. Low response rates make difficult ascertaining a population-based control group representative of the general population. Since no perfect control group was found, we choose two distinct control groups to test our hypotheses on populations presenting different aspects of the general population, as made by Stang et al. [49]. Controls from Group A and Group B present both advantages and weaknesses (see Table 2). Associations found consistently in the two control groups separately will strengthen our hypotheses, whereas inconsistent findings will provide new insights on potential confounding factors.

**Table 2 Tab2:** **Main advantages and weaknesses of the two control groups**

	Advantages	Weaknesses
Control Group A *(sperm donators & fertile partners of infertile woman)*	- Direct access to the subject (face to face recruitment & blood sampling)	- Older than cases/difficult to recruit subjects below 25 years old
	- More concerned by the topic/good participation rate	- Live with infertile woman/more exposed to reproductive toxicant than general population?
	- Sperm count available	
	- Regional recruitment	
Control Group B *(partners of pregnant woman hospitalized for pathological pregnancy)*	- Same age group than cases	- More difficult to approach (visit during evening/week-end)
	- Direct access to the subject (face to face recruitment & blood sampling)	
	- Presumably fecund	- No available serologies (need to store blood samples in separate areas)
	- Regional recruitment	- Link between subjects’ exposures partners’ pathological pregnancy?
	- Large population/easy to match with cases	

According to the TDS hypotheses, TGCT, cryptorchidism, hypospadias and several forms of male infertility are suspected to share common etiological factors [17, 18]. By choosing controls supposed to be fecund or having a normal sperm count, we aim to avoid subjects suffering from a minor form of TDS. In consequence, our controls are likely to be more fertile than the general population of the same age, and may present lower exposure to reproductive toxicants during postnatal periods. This should be taken into account in the interpretation of results when considering adolescent or adulthood exposure. Also, setting up a third control group, more representative of the general population (e.g. by selecting healthy young males from an existing cohort study conducted in France), may be considered.

The financial compensation for cases and controls participation will help recruitment, although the amount of compensation is kept low so subjects are not tempted to participate in the research against their personal convictions. Minimal information (age, occupation and reason for refusal) will be collected from subjects refusing participation to compare participants and non-participants and identify differential non-participation. Additionally, our study population may be compared to the general population based on data from the French National Institute for Statistic and Economic Studies (INSEE). This step will require coding all jobs according to the French classification of jobs and socio-economic categories from 2003 (PCS-2003).

Since prenatal information is of major interest to our research, we decided to include mothers of cases and controls in our study. Previous studies shown that mothers’ participation rate range from 54% to 71% [50, 51], which was similar to our pilot study [36]. Minimum information regarding parental occupation and residential addresses during the prenatal period is included in the case and control questionnaire to reduce missing data in case of mother’s non participation. Reliability of these items will be assessed by comparing information collected from participating case and control mothers and their respective sons.

Our biological sample collection will allow further ancillary projects. Heparinized plasma may be used to search for organic pollutants (multiresidue analyses) or biomarkers, whereas DNA samples will allow participating in genome wide association studies or perform DNA methylation studies. Biological samples will be made at the time of diagnosis, before any radio- or chemo-therapy (information recorded at time of the inclusion).

To reduce recall bias and to minimize missing data, we use objective criteria for exposure assessment when possible (job history analyzed by an industrial hygienist; use of GIS methods based on residential history). All subjects receive a document to gather information on residential and job history prior to the interview. The use of trained interviewers, blinded to the case or control status will ensure the same degree of questioning for both cases and controls.

A risk of misclassification for the GIS method remains due to imprecision in geocoding of residential addresses. Our pilot study allowed precise geocoding for 82% of all subjects’ residences. Lower precision was significantly associated with size of communes (<10,000 inhabitant), mainly related to rural addresses or hamlet lacking street numbers. No statistical difference in accuracy was found according to time period. In a recent French study, Semalgue-Faure et al. estimated that the medium imprecision of addresses when placed at the center of the hamlet or the street was about 200 meters [52]. Our geocoding accuracy was similar to this study [52], but slightly lower compared to several US studies [53–55]. However, geocoding of US addresses showed decreasing precision for older addresses [53]. Yet, imprecision does not lead to differential misclassifications. To improve ascertainment of the most accurate addresses, instructions have been given to interviewers on how to obtain complete addresses, or if not available, request ancillary information such as names of nearest intersecting roads or a nearby landmark still likely to be in place.

We expect our results to contribute to better understanding of the causes of TGCT and the rapid increase of its incidence. Thanks to the interdisciplinary network of research teams, we will be able to explore the effect of combined early and later-life pesticides exposure from multiple sources, as well as potential gene-environment interaction that have been poorly studied for TGCT. The use of GIS to assess environmental exposure to agricultural pesticide as well as the combination of environmental, domestic and occupational exposure are innovative and will improve exposure characterization. The thorough geocoding of subjects’ lifetime residential history will allow analyses of additional environmental risk factors in future studies as new hypothesis emerge. This research is an innovative approach in France that will contribute to improve our knowledge on the long term effects of pesticide exposure on human development, and potentially provide support for decisions in future healthcare policies.
